#### Inclusion criteria

The TRIC‐I‐HF‐DZHK24 trial was designed to enrol patients with evidence for right‐sided HF and underlying severe TR. All patients are deemed at high risk for tricuspid surgery as evaluated by the local heart team. All patients have symptomatic TR as defined by New York Heart Association (NYHA) class II, III, or IV. Enrolled patients have severe or greater TR (TR grade 3+: severe; TR grade 4+: massive; TR grade 5+: torrential) as assessed by TTE and TOE (*Table* *1*).^10^ Patients should satisfy qualitative and (new) quantitative criteria for graduation of TR severity. The anatomy of the tricuspid valve needs to be treatable with repair devices of TTVI with high likelihood for optimal technical outcome as assessed by local experience. Additional inclusion criteria facilitate the selection of patients with manifest HF in advanced disease stages of TR carrying an increased risk for HFH. All patients must have a history of HFH during the previous 12 months, or show evidence for cardio‐renal syndrome, or cardio‐hepatic syndrome. One of the three circumstances needs to be fulfilled. Cardio‐renal syndrome is defined by the presence of chronic kidney disease (estimated glomerular filtration rate <60 ml/min) in combination with severe or greater TR and evidence for HF. Chronic kidney disease should be attributed in the context of HF for qualification as selection criteria. Patients with chronic kidney disease due to age, hypertension, or diabetes without evidence for HF should not be selected. Cardio‐hepatic syndrome is defined by severe or greater TR and elevation of two out of the three following laboratory parameters: bilirubin, alkaline phosphatase, or gamma glutamyl transferase.^11^ An elevation of bilirubin is defined by values above 1.1 mg/dl. The cut‐off values of alkaline phosphatase and gamma glutamyl transferase are set by the laboratory of the local study sites, since upper limits vary between gender, age, and laboratory calibration. All inclusion criteria are listed in *Table* *2*.

**Table 2 ejhf3795-tbl-0002:** Study inclusion and exclusion criteria

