### Data collection

#### Baseline evaluation

Diagnostic procedures required for study screening are performed as standard of care. This includes TTE, TOE, right heart catheterization and assessment of the NYHA functional class. If a subject is determined as eligible study candidate and informed consent was obtained, several baseline examinations need to be performed. This baseline evaluation includes information on demographics and past medical history, electrocardiogram (ECG), physical assessment, medication, laboratory results, and assessment of standardized 6‐min walking distance test. QoL is assessed by the standardized Kansas City Cardiomyopathy Questionnaire (KCCQ).

In collaboration with the DZHK, a predefined set of biosamples is taken and included into a central biobank, if the subject agrees and specific informed consent was obtained.

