### Statistical analysis

A sample size of 224 patients in the interventional arm and 112 patients in the control arm (total of 336 patients) are required to achieve 85% power assuming a win ratio of 1.818 and a significance level of 5% for a two‐sided test. This assumes the proportion of wins is 0.4, the proportion of losses is 0.22, and the proportion of ties is 0.38. Assuming a drop‐out rate of 10%, a total of 360 patients must be randomized, 240 patients in the interventional arm, and 120 patients in the control arm. All analyses will be performed on the full analysis set according to the intention‐to‐treat principle. Further, sensitivity analyses according to the per‐protocol set will also be performed.

The two primary endpoints will be analysed in a hierarchical testing procedure. The second primary endpoint will only be analysed, if the first primary endpoint delivers statistically significant results. The first primary endpoint will be analysed using the Finkelstein and Schoenfeld method, which calculates a win ratio based on pairwise comparisons between all possible patient pairs from the two treatment groups. In each pair, a ‘winner’ is determined by hierarchical comparison: first, based on time to all‐cause mortality; if both patients are alive or die at the same time, then based on the number of HFH; and if still tied, based on change in KCCQ score at 12 months. The win ratio is defined as the total number of wins in the treatment group divided by the total number of losses. The statistical significance of the win ratio will be evaluated at a two‐sided alpha level of 5%. The second primary endpoint, event‐free survival (composite of all‐cause mortality and HFH), will be evaluated using a two‐sided log‐rank test stratified by TR grading at a significance level of 5%, provided that the first primary endpoint shows a statistically significant result as per the hierarchical testing procedure. Kaplan–Meier analyses will be conducted for both treatment groups, and event‐free probabilities will be reported at 1, 2, and 3 years of follow‐up.

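### The confirmatory log-rank test of the second primary endpoint is valid, but it leaves unused the baseline risk markers that the trial selects on and already records

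*Protocol article*

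**What the plan says.** The protocol article, Statistical analysis, compares event-free survival (death or HFH) by a two-sided log-rank "test stratified by TR grading at a significance level of 5" per cent, provided the first primary endpoint is significant. No other baseline variable is named for this test. The same section plans Kaplan–Meier analyses in both groups, with event-free probabilities at 1, 2 and 3 years.

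The sample size is derived for the first primary endpoint alone: 224 interventional and 112 control patients, 336 in all, "are required to achieve 85% power assuming a win ratio of 1.818". With drop-out allowed for, "a total of 360 patients must be randomized, 240 patients in the interventional arm, and 120 patients in the control arm". No event rate, hazard ratio, event count or power is given for the second primary endpoint.

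Under Inclusion criteria: "All patients must have a history of HFH during the previous 12 months, or show evidence for" cardio-renal or cardio-hepatic syndrome. One of the three is enough, and the article presents them as the means of selecting patients at raised risk of HFH. Under Baseline evaluation: "This baseline evaluation includes information on demographics and past medical history"; laboratory results are on the same list. Under Intervention scheme and trial flow, randomisation is 2:1, stratified by centre and TR grade.

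**The concern.** The article selects on three markers because it regards them as predictors of HFH, and HFH is part of this endpoint. Patients enter by different routes and with different numbers of markers, so risk is likely to vary within each TR grade. A time-to-event test that ignores strong predictors keeps its level but loses some power, and the unadjusted hazard ratio lies closer to 1 than the covariate-conditional one.

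This matters more here than usual. The Discussion rests the trial's claim of evidence on hard outcomes on this endpoint, yet its power is not stated. Recruitment has ended, so adding patients is no longer a simple remedy, whereas better use of data already collected still is.

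**Working it through.** **1. The plan's own figure.** Inputs from Statistical analysis: "the proportion of wins is 0.4, the proportion of losses is 0.22, and the proportion of ties is 0.38"; 85% power; "a significance level of 5% for a two‐sided test"; 2:1 allocation, so k = 2/3. The win ratio is 0.40/0.22 = 1.818. The Yu–Ganju formula is

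N = σ²(z₀.₉₇₅ + z₀.₈₅)² / (ln WR)², with σ² = 4(1 + p_tie) / [3k(1 − k)(1 − p_tie)].

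σ² = 4 × 1.38 / (3 × 2/3 × 1/3 × 0.62) = 13.355. N = 13.355 × 8.978 / 0.3573 = 335.6, rounded up to 336. The stated size reproduces, and it concerns the win ratio only.

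**2. Power of the second endpoint.** The article gives no inputs, so these are assumptions: 12-month control risk p_c of 25–45%, HR 0.60–0.75, all 360 patients followed. Schoenfeld:

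D = 240[1 − (1 − p_c)^HR] + 120p_c; power = Φ(√(2D/9) × |ln HR| − 1.96).

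Example with p_c = 35% and HR 0.65: the treated risk is 1 − 0.65^0.65 = 24.4%, D = 58.6 + 42 = 100.6, and power = Φ(4.728 × 0.4308 − 1.96) = 53%. For 80% power, 191 events would be needed.

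| Control risk | HR 0.60 | HR 0.65 | HR 0.70 | HR 0.75 |
|---|---|---|---|---|
| 25% | 51% | 40% | 30% | 22% |
| 35% | 66% | 53% | 41% | 29% |
| 45% | 77% | 64% | 50% | 36% |

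**3. Gain from adjustment, yes/no markers.** Simulation of 2,000 trials per row; 240:120 allocated within TR grade; 12-month censoring; HR 0.65. Also assumed: TR-grade shares 45/35/20% with hazards 1, 1.2 and 1.4; and marker prevalences of 50, 60 and 40% (prior HFH, renal, hepatic) before the entry rule. At least one marker is forced positive per patient, as the inclusion criteria require.

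| Marker HRs | Control risk | Stratified log-rank | Adjusted Cox | Difference (points) |
|---|---|---|---|---|
| 1, 1, 1 | 35% | 56.45% | 56.20% | −0.25 |
| 1, 1, 1 | 45% | 66.50% | 65.80% | −0.70 |
| 1.5, 1.3, 1.3 | 35% | 57.40% | 57.05% | −0.35 |
| 1.5, 1.3, 1.3 | 45% | 67.30% | 67.75% | +0.45 |
| 2, 1.5, 1.5 | 35% | 56.20% | 56.75% | +0.55 |
| 2, 1.5, 1.5 | 45% | 63.85% | 66.65% | +2.80 |
| 3, 2, 2 | 35% | 51.70% | 56.75% | +5.05 |
| 3, 2, 2 | 45% | 62.05% | 69.00% | +6.95 |

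The Monte Carlo standard error of each difference is 0.4 to 0.8 points.

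**4. Gain with continuous renal and hepatic values.** Entry rule enforced, control risk 40%, 1,500 runs per scenario. Marker HRs are for prior HFH and the two continuous markers.

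- HR 0.60, markers 1.5/1.2/1.2: 72.9% against 74.9% (+2.0).
- HR 0.60, markers 2.0/1.3/1.5: 71.9% against 76.3% (+4.4).
- HR 0.60, markers 2.5/1.4/1.6: 68.7% against 75.4% (+6.7).
- HR 0.65, markers 2.0/1.3/1.5: 57.0% against 60.1% (+3.1).

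A separate 3,000-run check with the entry rule gave 72.6% against 76.1% for HR 0.60 with the middle marker set, and 60.5% against 61.5% for HR 0.65 with weaker markers (1.5, 1.2, 1.2). A run whose stated inputs omit the entry rule gave a larger gain with the strongest set (67.6% against 76.6%). That should not be relied on, because a patient with no marker cannot enter.

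**5. Level and estimate.** Under no effect, three simulations rejected in 4.9%, 4.8% and 5.0% of trials with the log-rank test and in 4.7%, 4.6% and 5.3% with the adjusted test. With 1,500 runs the standard error at 5% is √(0.05 × 0.95/1500) = 0.6 points, so 5.3% is compatible with 5%. A conditional HR of 0.60 appeared as 0.61–0.63 without adjustment.

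**The case against.** The strongest reply is that nothing in the plan is wrong. A log-rank test stratified by a randomisation factor is standard and holds its level, and choosing an adjusted Cox model instead is a preference between accepted methods. The validity of the planned test stands in full. But the article fixes the confirmatory test, and that choice is less efficient if the markers predict as the article says they do.

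The size of the gain rests on assumptions, since the article gives no marker strength or prevalence. That also stands, and it is why a range including zero is reported.

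The proposed covariates do not match the syndromes exactly: a patient can meet the hepatic criterion without raised bilirubin, and the Limitations section concedes that the renal criterion may reflect other disease. This may reduce the gain but does not invalidate adjustment, which needs only baseline values fixed in advance.

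Changing a published primary analysis in an open-label trial after recruitment is more than a wording change. This has force and governs the timing of the fix.

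A reader might also infer that the plan yields no effect estimate because a log-rank test gives only a p-value. The documents do not support this. Event-free probabilities by arm are planned, a 12-month difference follows from them, and a hazard ratio may stand in the analysis plan, which is not shown.

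**Conclusion.** The point holds as one of efficiency. The planned test is valid but ignores recorded baseline markers that the trial itself treats as HFH risk factors, on an endpoint with no stated power. With the entry rule respected, the gain from adjustment is about 0 to 7 percentage points. It is close to nil for weak markers (between −0.4 and +2 points), about 5 to 7 points for the strongest sets tried, and under 1 point is lost if the markers are not prognostic. Type I error stays near 5%.

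All inputs for this endpoint are assumed, and drop-out is ignored, which flatters the power levels of both tests. Two further readings go too far. The difference between 0.60 and 0.61–0.63 is non-collapsibility of the hazard ratio, not bias in the test. Nor would adjustment rescue the endpoint: the adjusted test reached 80% power in none of the simulated scenarios.

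**What to change.** Before any comparison of outcomes by arm, and at the latest before database lock, specify the confirmatory test of the second primary endpoint as the two-sided 5% test of treatment from a Cox model stratified by TR grade. Its fixed covariates are HFH in the previous 12 months (yes/no), baseline eGFR and log baseline bilirubin. Add a simple rule for missing baseline laboratory values that does not depend on arm. Report the hazard ratio with 95% CI beside the planned Kaplan–Meier probabilities. Keep the log-rank test stratified by TR grade as a sensitivity analysis.

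No new data are needed. The costs are a modelling assumption for the covariates, a documented and dated change to a published analysis in an open-label trial, and a hazard ratio that is conditional on the covariates rather than marginal.

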**Inclusion criteria** Subject is symptomatic due to severe TR despite OMT for at least 30 days based on judgment of the local heart team. Subject is at intermediate or greater estimated risk of morbidity and mortality, defined as: Hospitalization for heart failure during the previous 12 months, or Cardio‐renal syndrome^a^, or Cardio‐hepatic syndrome^b^. NYHA functional class II, III or IVa. Femoral vein access and tricuspid valve anatomy are determined to be feasible for transcatheter tricuspid repair (including sufficient image quality by TTE and TOE). Age ≥18 years at time of consent. Subject must provide written informed consent prior to any study‐related procedure. **Exclusion criteria** Presence of severe aortic, mitral or pulmonary valve disease. Surgical or interventional treatment of the aortic, mitral or pulmonary valves within 60 days prior to randomization. Excessive pulmonary hypertension (sPAP >70 mmHg) or substantial pre‐capillary pulmonary hypertension (mPAP >30 mmHg + TPG >17 mmHg, or mPAP >30 mmHg + PVR >5 WU) as assessed by right heart catheterization. Tricuspid valve stenosis (tricuspid mean gradient >5 mmHg). Pacemaker or ICD leads, only if transvalvular leads impede successful transcatheter tricuspid repair. Prior tricuspid valve procedures or unfavourable anatomy for successful transcatheter tricuspid repair (e.g. significant calcification, Ebstein anomaly, large coaptation defect). Chronic renal failure requiring dialysis. Insufficient image quality of tricuspid valve by TTE and TOE. Myocardial infarction or cerebrovascular accident within 90 days prior to randomization. Life expectancy of less than 12 months

ICD, implantable cardioverter‐defibrillator; mPAP, mean pulmonary arterial pressure; NYHA, New York Heart Association; OMT, optimal medical therapy; PVR, pulmonary vascular resistance; sPAP, systolic pulmonary arterial pressure; TOE, transoesophageal echocardiography; TPG, transpulmonary gradient; TR, tricuspid regurgitation; TTE, transthoracic echocardiography; WU, Wood unit.

^a^
Chronic kidney disease with an estimated glomerular filtration rate <60 ml/min in combination with severe or greater TR and evidence for heart failure.

^b^
Elevation of two out of the three following laboratory parameters: bilirubin, alkaline phosphatase, or gamma glutamyl transferase; in combination with severe or greater TR and evidence for heart failure.

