#### Cross‐over procedure

Cross‐over from the control arm to the interventional arm is possible if several circumstances are met. First, cross‐over procedures can be performed only after a minimum period of 30 days after randomization. Second, the consideration of cross‐over procedures is only possible in subjects that already met the primary endpoint for unplanned HFH. Third, patients required intravenous diuretic therapy for the treatment of congested HF as surrogate for the severity of the associated HFH event. After the cross‐over procedure, patients remain in the study and are scheduled for follow‐up assessments as originally planned.

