#### Secondary endpoints

Secondary endpoints include all‐cause mortality, HFH (including frequency and length), change in QoL as assessed by KCCQ, re‐intervention for recurrent TR, change in NYHA functional class from baseline, change of 6‐min walking distance from baseline, change in echocardiographic parameters, change in peripheral oedema and subject weight, change of diuretic and HF medication from baseline, and change in laboratory markers for cardiac, renal and hepatic function. Sub‐group analyses are planned for different repair strategies. All endpoints are listed in *Table* *3*.

**Table 3 ejhf3795-tbl-0003:** Primary and secondary endpoints of the trial

**Hierarchical primary endpoint analysis** First primary endpoint: composite of all‐cause mortality, number of HFH, and lack of QoL improvement at 12 months. Second primary endpoint (tested only, if first primary endpoint is statistically significant): time to all‐cause mortality or HFH, whichever occurs first at 12 months.
**Secondary endpoints** All‐cause mortality Frequency and length of HFH Change in quality of life as assessed by KCCQ Re‐intervention rates for recurrent tricuspid regurgitation Change in NYHA class from baseline Change in 6‐min walk test distance from baseline Change in echocardiographic parameters (among others: TR grade, RV dimension and function, LV dimension and function, estimation of sPAP) Development of tricuspid stenosis (mean inflow gradient >5 mmHg) Change in peripheral oedema and subject weight Change in diuretic drugs and heart failure medications from baseline Change in laboratory markers for cardiac, renal and hepatic function
**Safety endpoint** Major adverse events related to the intervention during the first month, including mortality, life threatening bleeding (BARC classification type 3 and 5), major vascular or cardiac structural complications requiring intervention, or mechanical circulatory support.

BARC, Bleeding Academic Research Consortium; HFH, heart failure hospitalization; KCCQ, Kansas City Cardiomyopathy Questionnaire; LV, left ventricular; NYHA, New York Heart Association; QoL, quality of life; RV, right ventricular; sPAP, systolic pulmonary arterial pressure; TR, tricuspid regurgitation.

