Secondary endpoints will be compared between the study arms using explorative statistics. The explorative significance level will be set to 5% and no adjustment will be made for multiple testing. Baseline and follow‐up demographic data will be described using standard descriptive statistics including frequency distributions, means and standard deviations, and medians and interquartile ranges. Cumulative incidence for all‐cause mortality and HFH will be calculated and presented as Kaplan–Meier time‐to‐event curves with comparison of the control and interventional arm.

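### Re-intervention for recurrent TR falls under the general between-arm test, although controls can have it only after crossing over, so the comparison leans against TTVI whatever the durability of the repair

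*Protocol article*

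**What the plan says.** Table 3 of the protocol article (Secondary endpoints) lists "Re‐intervention rates for recurrent tricuspid regurgitation" and does not restrict it to patients who had TTVI. The Statistical analysis section then sets one rule for the whole list: "Secondary endpoints will be compared between the study arms using explorative statistics". It adds: "The explorative significance level will be set to 5% and no adjustment will be made for multiple testing". The analysis population is also fixed there: "All analyses will be performed on the full analysis set according to the intention‐to‐treat principle".

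Three other places decide who can have this event:

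- Table 2 excludes patients with "Prior tricuspid valve procedures or unfavourable anatomy for successful transcatheter tricuspid repair", so everyone enters without an earlier tricuspid procedure.
- The section on intervention scheme and trial flow schedules TTVI within 14 days of randomization in the interventional arm.
- The Cross-over procedure section gives controls a limited route to TTVI. Under its conditions, "cross‐over procedures can be performed only after a minimum period of 30 days after randomization" and "the consideration of cross‐over procedures is only possible in subjects that already met the primary endpoint for unplanned HFH". Intravenous diuretic treatment is also required. Crossed-over patients stay in follow-up.

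**The concern.** The words re-intervention and recurrent both require that the valve has been treated before. At randomization that holds for no patient in either arm. Soon afterwards it holds for nearly the whole interventional arm. In the control arm it holds only for those who qualify for cross-over, and only from the time of that procedure.

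The rule therefore compares an arm that is almost entirely at risk with an arm that is partly at risk, and later. If every repair were equally durable, the interventional arm would still be expected to show more re-interventions. The comparison mainly reflects who received a device. It says little about how well the device or the strategy worked. At stake is an exploratory p-value that could be read as a disadvantage of TTVI when it only reflects exposure.

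**Working it through.** **Inputs.** The plan gives 240 interventional and 120 control patients and a 5% level. It states no sidedness or test for this endpoint, so I take a two-sided Fisher's exact test as an illustration. The plan gives no re-intervention rate and no cross-over rate. Both are assumptions here and are shown as ranges. The plan has no figure of its own for this endpoint to reproduce.

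**Step 1: direction.** Let r be the re-intervention rate among treated patients, the same in both arms (equal durability), and s the share of controls who cross over. If all interventional patients are treated, the expected rates by intention to treat are:

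- interventional: r
- control: s × r

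The control rate is lower whenever s is below 1. With r = 5% and s = 20%, the expected counts are 240 × 0.05 = 12 and 120 × 0.20 × 0.05 = 1.2, that is 5% against 1%, although durability is identical. Crossed-over controls also have less time at risk, which this calculation ignores. Allowing for it would widen the gap.

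**Step 2: events needed for p < 0.05.**

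| Control events (of 120) | Fewest interventional events (of 240) | Two-sided p |
|---|---|---|
| 0 | 9 (9/240 = 3.75%) | 0.032 |
| 1 | 13 (13/240 = 5.4%) | 0.041 |
| 2 | 16 (16/240 = 6.7%) | 0.042 |

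With 0 control events, 8 interventional events give p = 0.056 and 12 give p = 0.010. With the 224 and 112 patients that the sample size calculation requires, the thresholds are again 9, 13 and 16 events.

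**Step 3: chance of a significant excess in the interventional arm under equal durability.** Interventional events are Binomial(240, r) and control events Binomial(120, s × r). The probabilities of all significant tables with the higher rate in the interventional arm are summed. For s = 0 this is simply P(X ≥ 9) with X ~ Binomial(240, r).

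| Re-intervention rate r | s = 0 | s = 20% | s = 50% |
|---|---|---|---|
| 1% | 0.1% | 0.1% | about 0% |
| 2% | 5.4% | 3.4% | 1.7% |
| 3% | 29.6% | 15.5% | 5.8% |
| 5% | 85.2% | 44.3% | 14.2% |
| 10% | about 100% | 84.6% | 32.7% |

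For reference, if all controls were treated (s = 100%), the chance at r = 5% would be 1.6%. The excess over that level comes from unequal exposure alone.

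**The case against.** The best defence has three parts.

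**The rule is a general sentence in a condensed article.** It names no test for this endpoint, and the analysis plan may restrict it to treated patients. It is true that the test is unnamed, and Fisher's test is only my illustration. But the article states the arm comparison and the intention-to-treat basis without exception. The point is a stated rule that does not suit one listed endpoint. It does not rest on missing detail.

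**Controls can have the event.** This stands. A reader might infer that the control count must be zero, or that the endpoint cannot be measured in that arm. The documents do not support this: "Cross‐over from the control arm to the interventional arm is possible if several circumstances are met", follow-up continues afterwards, and under intention to treat a later re-intervention counts in the control arm. A reader might also infer that the test must find harm. That is not supported either. Only the direction is built in. At rates of about 2% or less the test seldom reaches significance, and cross-over lowers the chance further.

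**The consequence is small.** This also stands. The comparison is labelled exploratory and lies outside both primary endpoints and the safety endpoint.

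One might go further and treat a control's first TTVI as the counterpart of a re-intervention, then test the two together. The documents do not make them equivalent. Cross-over is tied to a qualifying HFH, and no such condition is stated for re-intervention, so a combined endpoint would mix unlike events.

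**Conclusion.** The point holds as a minor one. As written, the plan compares re-intervention between arms that differ in exposure to the procedure the endpoint presupposes, so an excess in the interventional arm is expected even with equal durability. How often this would reach p < 0.05 depends on two rates that the documents do not give. Over the assumed range it runs from about 0% (1% rate) to about 100% (10% rate, no cross-over). A 5% rate with 20% of controls crossing over gives about 44%. These figures assume Fisher's test, full treatment of the interventional arm and one common rate in all treated patients. No primary conclusion is affected.

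**What to change.** Add an exception to the sentence on secondary endpoints in the Statistical analysis section, and carry it into the analysis plan before analysis:

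- Re-intervention for recurrent TR is not tested between arms. It is reported descriptively as a cumulative incidence among patients who had TTVI, timed from their first TTVI, with death as a competing event.
- First TTVI by cross-over in controls is reported separately, as a count and cumulative incidence from randomization, without a test.

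The cost is about one sentence and the loss of one exploratory arm comparison. Treatment, visits, sample size and the primary analyses do not change.
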